**Effect of polyethylene film and artificial teardrops versus normal saline on the incidence of superficial ocular disorders in unconscious patients: a prospective randomized triple-blinded three-arm clinical trial**

**Background:** Polyethylene covers are claimed to be useful in preventing ocular surface diseases (OSD); however, evidence of their clinical efficacy is limited. This clinical trial aims to compare the effect of polyethylene film and artificial teardrops versus normal saline on the incidence of OSD in unconscious patients. This paper summarizes the study protocol.

**Method:** The design of the planned study is a multicenter randomized blinded three-arm clinical trial. Although we need 25 patients in each arm, anticipating a total attrition rate of 20%, a total of 90 patients will be selected and included in the study, 30 patients for each arm. We will set up three arms ‘A’, ‘B’, and ‘C’ in which each eye of a patient will be considered for one of three interventions: artificial teardrops, polyethylene covers, or normal saline eye drops by tossing a coin. Then, each eligible patient will be allocated to one of the three arms by permuted block randomization. All patients are unconscious so, their blinding does not apply. Both the eye observer and the analyzer will be unaware of the type of interventions. The patients’ eyes will be examined based on the Corneal Fluorescein Staining Pattern. The collected data will be analyzed by SPSS-16 software at a 95% confidential level.

**Discussion:** The results of this study will contribute to the developing pieces of evidence for a safe, effective, and accessible eye care intervention for preventing the incidence of OSD in comatose patients.

**Keywords**: Coma, Infectious Diseases, Eye, Intensive Care Units, Nursing Care, Patients.

1. **Introduction**

The Ocular Surface Disease (OSD) is a common complication in patients who are admitted to Intensive Care Units (ICUs) but to receive minimal clinical consideration to prevent it [1, 2]. OSD is associated with different risk factors, as the impaired secretion and distribution of tear film over the ocular surface, tear components concentration due to lack of blinking, incomplete lid closure (lagophthalmos), and lid or conjunctival edema occurring with the use of a ventilator [3-8]. For these patients, there is a range of eye complications from mild conjunctival infections to serious everlasting ocular damage. Keratopathy (3.6% to 60%), chemosis (9% to 80%), and microbial keratitis are the most prevalent ocular disorders in ICU patients [9]. Insufficient eye care of ICU patients can increase the risk of serious eye problems such as corneal abrasions and ulceration, infectious keratitis, and even corneal perforation and loss of vision [10, 11].

- 1. ***Evidence-based Practice in Eye Care***

In recent decades, many pieces of evidence for eye care were developed; these practices include a wide range of interventions such as 1) washing the eyes with normal saline solution; 2) using lubricating ointments or teardrops; 3) moisturizing the chambers by applying a polyethylene eye cover (PEC), swimming goggles; 4) covering the eyes with eye shields, pads or patch; and 5) closing the eyelid with closure by transparent tape or tarsorrhaphy. There is no clear evidence as to which of these interventions represent the ideal eye care for ICU patients to prevent OSD [3, 4, 8, 10, 12-17]. There is confirmed that the healthcare professionals’ beliefs and traditions have played a major role in selecting eye care interventions in the ICU settings in different countries ICUs [4, 16]. Applying polyethylene eye covers has suggested as the most effective intervention [4] and the main components of the evidence-based protocol to prevent exposure keratopathy in the ICU settings [18]. But, in a very recent study of eye care for intensive care unit, the lubricants and taping of the lids are only advised for the conjunctival and corneal exposure [19]. The PEC was not considered as a part of the standard eye care for critically ill patients as well. So that, the standard care has been only comprised compromised a daily washing of eyelids with normal saline and sterile gauze and application of ocular lubricants at least twice per day in ICUs [20].

- 1. ***Critical Appraisal for Context***

In Iran, washing out eye discharge with sterile normal saline is considered as part of routine eye care for ICU patients, but this intervention is not well supported empirically and is no longer recommended worldwide. Our research team collaborated with health professionals to select alternative eye care interventions to prevent OSD in ICU patients. The team members carefully reviewed empirical and clinical literature to determine the effectiveness or benefits and risks of alternative interventions, while also considering their feasibility in the local ICU contexts. The results of this critical appraisal indicated the following: 1) Irrigating eye with sterile normal saline could cause an increase in the incidence of OSD and cross-infection, and the cotton wool balls can cause corneal scratching [4]. 2) lubrication materials could be hard and time-consuming to apply on a regular or frequent time intervals by nurses [21]; further, the ointment containers can be infected if not used properly. 3) Using eyelid sutures makes regular eye checkups difficult; the sutures are also unpleasant in appearance and block the eye activities [21]. 4) Tarsorrhaphy is also invasive and almost impossible to apply to our lagophthalmos patients. 5) Moisture chamber goggles are only designed for adults and are inconvenient to use when patients are in a supine position [21]. Securing the moisture chamber goggles around the head also increases the risk of edematous eyes in ventilated patients. 6) Mechanical closure of the eyes is recommended in case of the lagophthalmos [22]. 7) Polyethylene covers may be pulled by infants, children or agitated patients [21]. Lastly, eye covering is claimed as the most effective intervention in preventing exposure keratopathy [4].

After examining the benefits and risks of each eye care interventions and its feasibility in our ICU settings, the research team decides to use polyethylene film and artificial teardrops versus normal saline. However, evidence to support their clinical efficacy in reducing the incidence and severity of OSD is limited.

1. **Materials and methods**
   1. ***Aim***

The aim of this is to compare the effects of the polyethylene film and artificial teardrops versus normal saline on the incidence and severity of OSD in comatose patients admitted to the ICU.

- 1. ***Study design***

This is a prospective randomized triple-blinded three-armed clinical trial. We set up three arms ‘A’, ‘B’, and ‘C’ in which by tossing a coin, each eye of a patient will be allocated to one of three interventions: artificial teardrops, polyethylene covers, or normal saline eye drops. The groups will be as the following:

- Group “A”: patients received artificial teardrops for the left eyes and normal saline for the right eyes.
- Group “B”: patients received polyethylene cover for the left eyes and normal saline for the right eyes.
- Group “C”: patients received polyethylene cover to the left eyes and artificial teardrops to the right eyes.

Then, each eligible patient will be allocated to one of the three arms by permuted block randomization.

The study will be approved by the Research and Technology Vice-chancellor after confirming the proposal by the Research Ethics Committee at Hamadan University of Medical Sciences and registering in the Iranian Registry of Clinical Trials. We will conduct the study according to the ethical principles of the Helsinki Declaration of 2013 and follow the CONSORT 2010 statement (http://www.consort-statement.org). The study design is shown in Figure 1.

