**Figure 1 CONSORT flow diagram**

- 1. ***Sample size calculation***

The sample size is calculating according to the formula below.

$$n=\left[ \frac{\left( Z_{1-\alpha/2}\sqrt{p_{1}\left( 1-p_{1} \right)} \right)+\left( Z_{1-\beta}\sqrt{p_{2}\left( 1-p_{2} \right)} \right)}{d} \right]^{2}$$

With an 80% power and a 2-sided significance level of α = .05, and the probability of incidence of OSD of a study in which 3.6% (= p_1_) of patients had a positive fluorescein test in the simple eye ointment group and 20.2% (= p_2_) of patients had a positive fluorescein test in the eyelid taping group [5], the number of people needed in each group is 25. Anticipating a total attrition rate of 20%, a total of 90 patients will be included in the study, 30 patients for each arm.

- 1. ***Participants and recruitment***

Patients in the three ICUs in university-affiliated hospitals located in Malayer, Iran, will be recruited:

*2.4.1. Inclusion criteria*

- Newly being admitted to the ICUs;
- Having 18 years of age or older;
- Being comatose (with a Glasgow Coma Scale (GCS) less than or equal to 8 of 15);
- Undergoing mechanical ventilated;
- No trauma in the areas of the face and eyes;
- No history of chronic disease, electrolyte imbalance, cataract surgery or glaucoma;
- Absence of blinking (less than five times per minute); and
- Having a healthy cornea.

*2.4.2. Exclusion criteria*

- Presence of consciousness or natural blinking reflexes;
- Requiring cardiopulmonary resuscitation during the trial;
- Getting discharged from ICUs to the other centers or death.
  1. ***Implementation of the Interventions***

All patients will be received routine eye care. Routine eye care is consisted of eye irrigation with sterile normal saline when necessary (PRN) in all our ICUs. In addition to this usual care, prior to applying the planned interventions, the participants’ eyelids and surrounding skin will be gently irrigated by sterile normal saline and sterile gauze in the same way. The interventions are as below:

- For the intervention with artificial teardrops, while pulling down the lower lid of the patient’s eye to form a V pocket, two Tearlose (Miscellaneous) drops will be applied every six hours.
- For the intervention with normal saline, two drops of saline 0.9% will be applied in the same manner and dose.

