- For the intervention with a polyethylene eye cover, 2.5-inch square pieces of thin plastic film will be put from the above of the eyebrow to the cheekbone and fixed by hypoallergenic paper tape.
  1. ***Outcome***

Assessments will be conducted using the statistical software SPSS version 16.0 for windows (SPSS Inc., Chicago, IL), setting the p-values at < 0.05. The measures used and measurements in the study are described in Table 1.

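### The trial is called triple-blinded but names only two blinded roles, and a taped film with fixed sides leaves the observer's blinding asserted, not secured

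*Protocol*

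**What the plan says.** The Study design section opens: "This is a prospective randomized triple-blinded three-armed clinical trial". The title and the Discussion use the same label; the Method paragraph of the abstract says only that the trial is blinded.

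That Method paragraph is the one place that says who is blind. On patients: "All patients are unconscious so, their blinding does not apply". On the others: "Both the eye observer and the analyzer will be unaware of the type of interventions".

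The Study design section lists the arms:

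- Arm A: "patients received artificial teardrops for the left eyes and normal saline for the right eyes"
- Arm B: "patients received polyethylene cover for the left eyes and normal saline for the right eyes"
- Arm C: "patients received polyethylene cover to the left eyes and artificial teardrops to the right eyes"

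Figure 1 repeats these sides, with 30 patients per arm. The abstract and the Study design section also mention a coin toss for allocating the eyes.

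Under Implementation of the Interventions, "thin plastic film will be put from the above of the eyebrow to the cheekbone and fixed by hypoallergenic paper tape". For saline, "two drops of saline 0.9% will be applied in the same manner and dose", that is, as for the teardrops. Under Primary outcome (2.6.1), punctate erosions are counted at the slit lamp some minutes after fluorescein. Table 1 places these readings at baseline (T0) and at day 5 (T1).

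**The concern.** The label promises more than the text describes. A reader of the title will take it that three parties are blind; the protocol names two and sets the patient aside.

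Of those two, the observer matters more, because the primary outcome is that person's visual count. A film taped over one eye is obvious until it is removed, and only film eyes are taped. The protocol does not say who takes the film off, when, or whether the observer is absent. The fixed sides add to this: an observer who knows the design learns something about treatment simply from which eye is being examined.

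At stake is the grading near the threshold. Grade 0 is no erosion and grade 1 starts at a single erosion, so a doubtful spot decides the grade. The Introduction reports film as claimed to be the most effective option and saline as possibly harmful, so an observer could hold an expectation about direction.

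**Working it through.** The protocol gives no figure to reproduce here. The check is a count of roles and a tabulation of what side reveals.

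**1. Roles.** Label: three. Stated as unaware: observer and analyzer, so 2. Patients: declared not applicable. Bedside nurses: not mentioned, and a nurse who tapes film on one eye and puts drops in the other cannot be unaware. Total described: 2.

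**2. Treatment by arm and side** (Study design, Figure 1; 30 patients per arm):

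| Arm | Left eye | Right eye |
|---|---|---|
| A | teardrops | saline |
| B | film | saline |
| C | film | teardrops |

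Each of the 6 arm-by-eye cells holds exactly one treatment.

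**3. What side alone reveals** (planned eyes):

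| Side | Film | Teardrops | Saline | Total |
|---|---|---|---|---|
| Left | 30 + 30 = 60 | 30 | 0 | 90 |
| Right | 0 | 30 | 30 + 30 = 60 | 90 |

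Overall, film eyes are 60/180 = 1/3. Given a left eye the share is 60/90 = 2/3; given a right eye it is 0. For saline it is 0 on the left and 60/90 = 2/3 on the right. Side therefore excludes one treatment for all 180 eyes, even if every trace of film has gone.

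**4. If sides were randomised per patient.** Three arms times two orientations give 6 equally likely patterns. The left eye has film in one orientation of arm B and one of arm C, so 2/6 = 1/3, and likewise for each other treatment and for the right eye. Side then carries no information.

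**5. What sight of the film reveals.** At T1, film or tape traces identify that eye's treatment and show that the arm is B or C. Fluorescein has to go in at least four minutes before the reading, so the film must be off the eye by then. The text does not say who removes it or who instils the dye.

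**6. Contrasts exposed.** Film versus saline (arm B) and film versus teardrops (arm C) are two of the three within-patient contrasts. Arm A compares two kinds of drop given in the same manner and dose, so it offers the observer no comparable visible cue.

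**The case against.** The strongest reply is that the protocol does state that observer and analyzer will be unaware, and that silence about the method is not proof of failure. The film must come off before the dye is instilled, so someone other than the observer may well remove it. This stands in part: blinding the observer is feasible. It does not dispose of the point, because the fixed sides are a written rule, not an omission, and they inform any observer who knows the design.

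One could also count unconscious patients as the third blinded party, since they are unaware in fact. The protocol itself says that blinding does not apply to them. Nor does it claim that the nurses are blind, so their knowledge contradicts nothing except the count in the label.

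Three stronger readings are tempting, and the documents do not support them:

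- **That neither role is blind.** The protocol asserts both. What can be shown is that observer blinding lacks a described safeguard and is weakened by the fixed sides.
- **That the analyst is certainly unblinded.** Arm letter plus eye does give the treatment in all 6 cells, but the protocol does not say what the analysis file contains, and its coding may be settled elsewhere. This part is conditional.
- **That a few biased readings would produce a positive result.** In an exact two-sided McNemar test, 6 discordant pairs to 0 give 2 × (1/2)^6 = 0.031, while 5 to 0 give 0.0625. That assumes no opposing pair: 7 to 1 gives 2 × (1 + 8)/2^8 = 0.070, and it takes 8 to 1, 2 × (1 + 9)/2^9 = 0.039, to pass. Nothing in the protocol says how many readings would be biased.

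The expectation of a film benefit should not be pressed either. The same Introduction calls the evidence limited, and the sample size uses a two-sided test.

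**Conclusion.** The concern holds in this form. The label triple-blinded does not match the two roles described. Observer blinding is claimed but not secured, for two reasons: no step keeps the taped film out of the observer's sight at T1, and the fixed sides exclude one treatment for each of the 180 planned eyes. The exposure falls on the contrasts in arms B and C. Its effect on the result cannot be quantified from the protocol.

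This rests on two assumptions: that the observer knows the design or sees the film or its traces, and that the listed groups and Figure 1, not the coin toss, determine the sides. If the toss was meant to set sides for each patient, the side argument falls away, but the group list and Figure 1 would then be wrong and need correcting. Saying that one erosion can decide incidence further assumes that any grade above 0 counts as incident disease. Who is blind, and by what means, belongs in the protocol. The change should be made; it does not call for a new design.

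**What to change.** 1. Replace triple-blinded with observer- and analyst-blinded in the title, the Study design section and the Discussion. This is accurate only together with the steps below.
2. State that at T1 the bedside nurse, not the observer, removes film and tape and cleans the skin around both eyes of every patient before the observer arrives. Doing this for all patients and both eyes means that the preparation itself reveals nothing. Skin marks after days of taping may persist, and the report should acknowledge this.
3. Allocate the side of each treatment at random per patient, as the coin toss suggests, and correct the group list and Figure 1 to match. Side then no longer reveals treatment.
4. If the analysis file would otherwise carry arm letter and eye, give the analyst neutral treatment codes. If sides stay fixed, also withhold the side column: a code that appears only on left eyes would be film, and one only on right eyes would be saline.

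Cost: a few minutes of existing nurse time at the single T1 examination, a side-allocation list, a recoded file and the wording changes.

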**Assessment of eligibility (n=…)**

## Permuted block randomized allocation (n=90)

## (T0)

## Baseline measurement

**Arm** **C** (n=30)

- Received polyethylene cover (Left eye) & artificial teardrops (Right eye)

**Arm** **A** (n=30)

- Received artificial teardrops (Left eye) & normal saline (Right eye).

**Arm** **B** (n=30)

- Received polyethylene cover (Left eye) & normal saline (Right eye)

Analyzed (n=30)

Analyzed (n=30)

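### The arm definitions fix which eye gets which treatment, against the coin-toss wording, so every within-patient contrast carries any left-right difference in full

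*Protocol*

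**What the plan says.** The Study design section first describes an eye-level coin toss: "by tossing a coin, each eye of a patient will be allocated to one of three interventions". The abstract has a similar sentence. The section then lists the three groups with a side attached to each treatment. The entry for the second group (B) reads "patients received polyethylene cover for the left eyes and normal saline for the right eyes". The other two entries follow the same pattern: A has teardrops on the left with saline on the right, and C has the cover on the left with teardrops on the right. After the list comes the patient-level step: "each eligible patient will be allocated to one of the three arms by permuted block randomization". Figure 1 shows the same sides for all three arms; its box for B, for example, reads "Received polyethylene cover (Left eye) & normal saline (Right eye".

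The Data Analysis section compares incidence by McNemar's test, a paired test, and mentions no term for eye side. On blinding, the abstract states: "Both the eye observer and the analyzer will be unaware of the type of interventions".

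**The concern.** In a design where one patient carries two treatments, the within-patient comparison is protected only if chance decides which eye gets which treatment. Randomising the patient to an arm does not do this when the sides inside each arm are already set. A left-right difference then has the same sign in all three arms, and adding patients does not average it out.

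Cover versus saline is the most exposed comparison, because the two never share a side. If right eyes did worse for reasons unrelated to treatment, saline would look worse than both alternatives; if left eyes did worse, a real benefit could be hidden.

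The coin-toss sentences do not settle the matter. A toss made once to build an arm's template leaves side fixed for every patient. A toss made for each patient would contradict the group list and Figure 1.

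**Working it through.** The plan states no figure to reproduce on this point. The check has three steps.

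**1. Treatment by side.** From the group list and Figure 1, at 30 patients per arm:

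| | Cover | Teardrops | Saline drops |
|---|---|---|---|
| Left eyes | 60 (B, C) | 30 (A) | 0 |
| Right eyes | 0 | 30 (C) | 60 (A, B) |

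**2. What McNemar's test sees.** I read the planned test as a paired comparison within each arm. Inputs: 25 pairs (the protocol's number per group), two-sided 0.05, exact test. Assumptions: no treatment effect, independent eyes, left incidence a, right incidence b. The discordant probabilities are a(1−b) and b(1−a). With side randomised, each becomes the mean of the two.

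- 15% v 25%: 0.15 × 0.75 = 0.1125 and 0.25 × 0.85 = 0.2125; randomised, 0.1625 each.
- 10% v 30%: 0.10 × 0.70 = 0.07 and 0.30 × 0.90 = 0.27; randomised, 0.17 each.

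| Left v right incidence (assumed) | Rejection, sides fixed | Rejection, side randomised |
|---|---|---|
| 20.2% v 20.2% | 0.019 | 0.019 |
| 15% v 25% | 0.069 | 0.019 |
| 10% v 30% | 0.277 | 0.020 |

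With all 30 pairs the fixed-side values for the last two rows are 0.089 and 0.358.

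**3. The cost of adjusting afterwards.** Write P, T, S for cover, teardrops and saline, and s for an additive left-minus-right effect. The arms' mean left-minus-right differences estimate

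A = (T−S)+s, B = (P−S)+s, C = (P−T)+s.

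Hence s = A − B + C, P−S = 2B − A − C, T−S = B − C and P−T = B − A. In units of the variance of one arm's mean difference:

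- Side ignored, three arms pooled by least squares: 2/3 for each contrast.
- Side in the model, sides fixed: P−S has 4 + 1 + 1 = 6; T−S and P−T have 1 + 1 = 2.
- Side in the model, sides balanced within arm: 2/3 again.

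Using within-patient differences only, the inflation is 6 ÷ (2/3) = 9 for P−S and 2 ÷ (2/3) = 3 for the others.

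Patients are randomised to arms, so the arm means of the two-eye sums also carry information: C − A estimates P−S, C − B estimates T−S and B − A estimates P−T, all free of s. Sums and differences are uncorrelated when the eyes have equal variance. For inter-eye correlation ρ their variances are in the ratio (1+ρ):(1−ρ). Combining both by generalised least squares, the inflation from adding side reduces to

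- P−S: 3(2+ρ)/(2−ρ)
- T−S and P−T: 3/(2−ρ)

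| ρ (assumed) | P−S | T−S, P−T |
|---|---|---|
| 0 | 3 × 2/2 = 3 | 1.5 |
| 0.5 | 3 × 2.5/1.5 = 5 | 2 |
| 0.8 | 3 × 2.8/1.2 = 7 | 2.5 |
| limit at 1 | 9 | 3 |

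**The case against.** **The coin toss may be per patient.** The sentences can be read that way, with the group list as loose wording. This stands as far as it goes: the documents hold a contradiction, and a reader should not infer that confounding is settled fact. Fixed sides are still the likelier reading, because the list and the figure agree and the only randomisation placed after the toss is of patients to arms.

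**No side difference is documented.** This is correct. The risk factors in the Introduction, such as reduced blinking and incomplete lid closure, are not described as affecting one side more. A reader might infer that a bias is present; the documents show only that the design would not protect against one. An assumed 10-point gap also inflates the error modestly (0.069 against a nominal 0.05); serious inflation needs something like 20 points.

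**Side can be adjusted for, and the loss is not nine-fold.** Teardrops appear on both sides, so s is estimable under additivity. Nine is the ceiling of a within-patient analysis and should not be quoted as the cost. An analysis plan not shown here might contain such an adjustment. It would still pay at least a three-fold variance for cover versus saline, because the allocation is the cause.

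**Blinding.** A reader might infer that side unblinds the observer. No passage says that the observer knows the arm scheme. One who did could rule out saline drops in left eyes and the cover in right eyes, but would still face two candidate treatments for each eye. This is a secondary, conditional point.

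**Saline reaches left eyes too.** Routine irrigation and lid cleaning use saline in all patients, so the accurate statement is that no left eye is assigned saline drops.

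**Conclusion.** The point holds in this form. The protocol's coin-toss sentences conflict with its arm definitions and Figure 1. On the definitions as written, side is not randomised per patient, and the planned paired test cannot tell a treatment effect from a side effect.

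The bias in each within-arm contrast equals the whole left-right difference, whose size the documents do not give. The rejection probabilities above rest on assumed incidences and independent eyes. The variance factors rest on an additive side effect, equal variances and assumed inter-eye correlations. The structural conclusion needs none of these. It should be corrected in the allocation, since analysis alone can repair it only by giving up precision.

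**What to change.** Reconcile the coin-toss sentences in the abstract and the Study design section with the group list and Figure 1. Replace the toss with one permuted-block list of six cells: three treatment pairs by two side orders. Blocks of 6 fit the planned total (90 ÷ 6 = 15 blocks, so 15 patients per cell); blocks of 12 would not (90 ÷ 12 = 7.5). Each patient is then randomised both to a pair and to which eye receives which member.

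In the Data Analysis section, keep McNemar's test within each pair, where randomisation now protects it. McNemar's test takes no covariate, so add a side-adjusted paired analysis, for example conditional logistic regression or GEE with treatment and side. In the linear working above, this adjustment costs no precision once sides are balanced.

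If enrolment has begun, apply the new list to the remaining patients and report the side-adjusted contrast with its loss of precision.

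Cost: a new allocation list, changed wording in the four places named, and nurses following a side order set per patient instead of per arm. No extra patients or visits are needed.
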